#### Street theatre

The purpose of the street theatre is to allow large numbers of community members to be exposed to messaging that focuses on gender equity, and to encourage them to interact with the issues through the drama. A professional theatre company will be hired to script and direct a short, interactive, play. The play will be performed in one intervention site in each of the 12 districts and will also be professionally recorded so that other communities without access to live performances can view the screenings.

#### Community/religious leader workshop

Community leaders will be trained in a 2 day workshop designed to: 1) introduce the project 'Change Starts at Home’ to key stakeholders who are knowledgeable and supportive of the project 2) facilitate smooth implementation of project activities by getting community leader buy-in; 3) strengthen ties between EA/VDRC and the religious/community leaders to encourage better coordinated responses to violence against women, especially IPV in the targeted communities; and 4) provide a forum for the religious and community leaders to reflect on their own position and capacity to comprehend and respond to VAWG, especially IPV. During this workshop the leaders will generate an action plan designed to contribute to violence prevention and enhanced response to partner violence in their local communities; this action plan will be followed up by VDRC after 6 months. The religious community / religious leaders and their local LDG will also be encouraged to organize a joint event during phase III.

### Control group

The control group participants will be exposed to the radio program only, and will not participate in the LDGs, nor will they or their family members participate in the workshops and community activities. At three separate time points, a randomly selected sample of female community members who meet inclusion criteria will be invited to take a survey. To adhere to international standards of ethics surrounding conducting research with violence against women, female participants in the control group will be provided with the same referrals to free or low-cost resources as those in the intervention group [37].

### Intervention adherence

Intervention adherence is monitored through a number of mechanisms including:The submission of weekly forms by the LDG facilitators, which includes attendance and an assessment of the conduct of the group;Audio calls placed by Equal Access staff (at least 1 male and 1 female) to obtain more in-depth feedback on the conduct of the group;Review of between 2 and 6 audio recordings of LDG sessions by Equal Access staff;In-person support and monitoring visits by VDRC field officers to between 4 – 5 LDGs weekly; andBooster trainings for LDG facilitators every 6 weeks.

### Concomitant interventions

The study team attempted to choose VDCs where other projects were not occurring or forthcoming prior to baseline. However, development aid to Nepal, especially following the earthquake in 2015, is not within the control of the current investigation. Study participants are not disallowed participation in other programs as withholding opportunities for material or other support would be potentially unethical and would not serve the underlying goals of *Change*. Therefore, the study team will monitor local, national, or international projects that might begin operating during the study period in all of the study communities. Further, a member of the National Health Research Council is among the study’s scientific advisory board, providing an opportunity to learn about other projects that are forthcoming, as all health-related projects require approval from the council to operate in the country.

### Outcomes

The primary and secondary outcomes, and covariates are assessed through an interview-administered survey at baseline, 12 months’ post-baseline and 18-months post baseline. Scale items and their sources are listed in Table 2.

**Table 2 Tab2:** Outcomes and other measures for the change starts at home project

Outcomes	Source
Primary	
Physical and / or sexual intimate partner violence in prior 12 months	Standard Outcomes for Assessment of Intimate Partner Violence for What Works to Prevent Violence Global Program [49]
Secondary	
Psychological partner abuse in prior 12 months	World Health Organization Multi-Country Study (WHO MCS) on Women’s Health and Domestic Violence [50]
Economic partner abuse in the prior 12 months	United Nations Multi-country Study on Men and Violence [51]
Conflict and conflict resolution techniques in prior 12 months	Index of items from several studies. Item on quarrelling from WHO MCS [50]; two items adapted from the Relationship Self Efficacy Beliefs’ Scale [52]
Couple communication in prior 12 months	WHO MCS [50]
Attitudes toward gender equity	Adapted Gender Equitable Men (GEM) scale [53]
Attitudes toward the acceptability of intimate partner violence	Adapted GEM scale [53]
Perceptions of community-norms on the acceptability of partner violence	Developed for study
Other Measures	
Socio-demographics	Developed for the study
Help-seeking for IPV	Developed for the study
Exposure to violence from natal and marital family members	Developed for the study
Depressive symptoms	PHQ-8 [54]
Disability	Washington Group on Disability Statistics [55]
Exposure to messages on VAWG	Developed for the study
Participant reaction to the study	Reactions to Research Participation Scale [56]

### Quality control and data entry

Data quality procedures are outlined in the field manual in detail and include the selection of enumerators who have prior experience collecting data on sensitive topics, with special emphasis on VAWG, extensive classroom and field training and practice, pilot testing of the data collection application to limit data collection and entry errors, and direct observation, visual checks of the application entries, and in-person and telephone contact with a subset of entries to ascertain the veracity of the data collected. Daily field team debriefings and back-end data quality checks by the data collection firm and study team are used to identify and rectify errors in a timely manner. An audit trail will be kept of all changes made during data cleaning. After the first round of cleaning is complete, typically within one month of data collection, no further changes to the database will be allowed.

### Qualitative instruments

The overall goals of the qualitative assessments are to examine pathways through which outcomes of interest may be impacted by the *Change* Intervention and to assess contextual factors influencing intervention effectiveness. These will be achieved through in-depth interviews with participating couples and focus group discussions with LDG members’ family members and community leaders. The specific qualitative approach, research goal, audience, and time point have been summarized in Table 3.

**Table 3 Tab3:** Schedule of qualitative measurements and objectives

Audience	Time Point	Qualitative Approach	Objectives
Couples in LDGs	Prior to the commencement of programming, midpoint, program end line, and 18 month follow-up	18 In-depth interviews each measurement occasion	To understand changes in knowledge, attitudes and behaviours, environmental facilitators and constraints to the couple exhibiting more gender equitable attitudes and behaviours, and the degree and impact of their activism within their community.
Family Members of LDG participants	Prior to the commencement of programming and program endline	12 Focus group discussions each measurement occasion	To understand changes in family-based norms on gender equity and intimate partner violence, and the impact of any project activities and couple-based activism they may have been exposed to.
Community Leaders	1st quarter of the project and 6 months thereafter	3 Focus group discussions each measurement occasion	To examine changes in their attitudes on gender equity and intimate partner violence, community norms on gender equity and intimate partner violence, contextual factors that are occurring in the community, and the impact of the project at the community level.
Radio Listeners	Quarterly	IVR/SMS listener feedback analysis	To examine change over time in community norms on gender equity and IPV.
LDG Members	1^st^ month of programming, midpoint, and program end line	6 LDG groups followed over 3 time points	To investigate change over time in attitudes and group norms on gender equity and IPV, and how the group process may facilitate these changes.

### Sample size and power

This study is powered to detect meaningful differences in prevalence of IPV. To calculate study power, we took into consideration the number of experimental conditions, the number groups/clusters nested within conditions, the number of persons within groups, the intra-class correlation coefficient (ICC), within-group over time correlations, and traditional variance components [38]. We have 36 units of randomization (VDCs) and 40 randomly sampled persons within each unit, 20 in each of two selected VDC sub-units called wards. Assuming a conservative over-time group-level correlation of 0.40, a 12-month prevalence of physical or sexual IPV of 14%, which was based on estimates from the 2011 Demographic and Health Survey in Nepal [2]. a conservative standard deviation of 25%, a conservative intra-class correlation of 0.05, with 80% power and 5% alpha (2 sided test) the study can detect a difference in percentage of 7%.

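### The 7-point detectable difference depends on a standard deviation of 25%, but a yes/no outcome at 14% has one of 34.7%, so the stated 80% power is not there

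*Protocol article*

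**What the plan says.** All the inputs stand in one paragraph of the protocol article, Sample size and power:

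- Prevalence: "a 12-month prevalence of physical or sexual IPV of 14" per cent.
- Spread and clustering: "a conservative standard deviation of 25%, a conservative intra-class correlation of 0.05".
- Correlation over time: "Assuming a conservative over-time group-level correlation of 0.40".
- Size: "We have 36 units of randomization (VDCs) and 40 randomly sampled persons within each unit".
- Result: at 80% power and two-sided 5% alpha, "the study can detect a difference in percentage of 7" percentage points.

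Table 2 (Outcomes) defines the primary outcome as physical and/or sexual IPV in the past 12 months, which each woman either has or has not experienced. The Statistical analysis section plans logistic mixed models in which the effect is the interaction of time and condition, that is, the between-arm difference in change from baseline.

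**The concern.** The prevalence and the standard deviation cannot both be chosen freely. A 0/1 variable with mean p has variance p(1 − p), so fixing 14% fixes the standard deviation as well. The 25% does not match, and it errs in the favourable direction: it is slightly below even the value at 7% prevalence (25.5%), which is the least variable of the four arm-by-time cells if the full effect occurs.

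At stake is the headline power claim. Taken as a reduction, 7 points from 14% is a halving of IPV. If the design has little more than an even chance of detecting that, a null result says much less than a reader who trusts the stated 80% would think. The Discussion expects the results to be put to use at once by governments and donors, so such a misreading would have consequences.

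**Working it through.** **Inputs.** From Sample size and power: p = 0.14, SD = 0.25, ICC = 0.05, r = 0.40, m = 40 women per VDC per round, 36 VDCs. From Pair-matching: one VDC of each pair goes to each arm, so g = 18 per arm. The multiplier for 80% power at two-sided 5% is 1.960 + 0.842 = 2.802 (normal), or 2.885 with t on 36 − 2 = 34 df. The design effect is 1 + 39 × 0.05 = 2.95.

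**1. The SD that goes with the prevalence.**
- At 14%: √(0.14 × 0.86) = √0.1204 = 0.347.
- At 7%: √(0.07 × 0.93) = √0.0651 = 0.255.
- Solving p(1 − p) = 0.0625 gives p = 0.067, the prevalence that an SD of 25% implies.
- Variance ratio: 0.1204 / 0.0625 = 1.93.

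**2. Reproducing the stated 7 points.** For the difference in change between arms, with r applied to the VDC means:

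Var = 4 × SD² × 2.95 × (1 − r) / (m × g)

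With SD 0.25: 4 × 0.0625 × 2.95 × 0.60 / 720 = 0.000615, so SE = 2.48 points. The detectable difference is 2.802 × 2.48 = 6.95 points (normal) or 2.885 × 2.48 = 7.15 (t). Power for 7 points is 81% or 78%. This matches the article.

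**3. Changing only the SD.** 4 × 0.1204 × 2.95 × 0.60 / 720 = 0.001184, so SE = 3.44 points. The detectable difference is 9.64 or 9.93 points. Power for 7 points is Φ(7/3.44 − 1.96) = 53%, or 51% with t.

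**4. Giving each cell its own variance.** With three cells at 14% and the treated follow-up cell at 7%, the mean variance is (3 × 0.1204 + 0.0651)/4 = 0.1066. SE = 3.24 points.

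**5. Applying r to the VDC component only.** The article calls 0.40 a group-level correlation, so this is a fair literal reading:

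Var = 4 × SD² × [0.95 + 40 × 0.05 × 0.60] / 720 = 4 × SD² × 2.15 / 720

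At SD 0.25 this gives 7.65 to 7.88 points, a poorer match to 7 than step 2.

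| Variance used | r applied to | SE (points) | Detectable difference, normal / t | Power for 7 points, normal / t |
|---|---|---|---|---|
| SD 25% (as stated) | VDC means | 2.48 | 6.95 / 7.15 | 81% / 78% |
| SD 34.7% | VDC means | 3.44 | 9.64 / 9.93 | 53% / 51% |
| Cells at 14, 14, 14, 7% | VDC means | 3.24 | 9.07 / 9.34 | 58% / 56% |
| SD 34.7% | VDC component | 3.79 | 10.62 / 10.94 | 46% / 43% |
| Cells at 14, 14, 14, 7% | VDC component | 3.57 | 10.00 / 10.29 | 50% / 48% |

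**6. Reading 25% as a between-VDC SD.** This does not help: 0.25 × √(2/18) × 2.802 gives a detectable difference of about 23 points, even at a single time point.

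**The case against.** The strongest reply is that the article does not print its formula and refers to a source for the method, so the variant in step 2 is identified only by its match to 7. Other readings shrink the gap:

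- A comparison at follow-up only, Var = 2 × SD² × 2.95 / 720, gives 6.3 to 6.7 points at SD 25%, some of which also round to 7. With the variance averaged over 14% and 7%, its power for 7 points is 67 to 72%.
- A baseline-adjusted comparison with the same averaged variance reaches 77 to 79%. At SD 25%, however, it would have given 5.8 to 6.0 points (normal or t on 34 df).
- One variant does reach 80%: the averaged variance, r on the VDC component, and no doubling for the baseline round. At SD 25% it gives 5.4 to 5.7 points, so it is not what the authors computed.

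None of these is the time-by-condition contrast in the Statistical analysis section, and none makes 25% conservative. What stands is that the size of the shortfall depends on the formula; its direction does not. It is also fair that the lowest power figures (43 to 46%) come from the reading that reproduces 7 less well.

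A second reply concerns prevalence. The Population section says these districts lie in the region with the highest IPV prevalence, so the true figure may exceed 14%. For a fixed 7-point difference, which is what the article states, that lowers power: about 45% at a prevalence of 20% (step 4 formula, normal). For a halving it raises power, to about 76% at 20%. The effect must therefore be named before a higher prevalence can be called better or worse.

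Pair-matching might recover some precision, but the article gives no figure for it and does not list it among the inputs.

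**Conclusion.** The statement is wrong as written. An SD of 25% contradicts the 14% prevalence in the same sentence, is too small, and drives the 7-point result. For the planned change-from-baseline contrast, with all other inputs kept, the design detects about 9 to 11 points with 80% power (9.1 to 10.9 in the table). Its power for a fall from 14% to 7% is about 43 to 58%. For scale, reaching 80% for 7 points under step 3 would take about 18 × (9.64/7)² ≈ 34 VDCs per arm rather than 18.

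These figures assume equal cluster sizes, an ICC of 0.05 in every cell, no gain from matching, and a normal or t approximation on the risk-difference scale in place of the logistic model. That the SD is too small needs only the prevalence and the binary outcome.

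**What to change.** In Sample size and power:

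1. Replace the 25% with the binomial value, √[p(1 − p)], stating the prevalence assumed in each arm and round, and stop describing the SD as conservative.
2. Restate the result for the planned contrast: about 9 to 11 points detectable with 80% power or, equivalently, about 43 to 58% power for 7 points. Give the formula and say whether 0.40 applies to the observed VDC means or to the VDC component, since this moves the figure by about one point.
3. Recompute with the prevalence and ICC from the baseline survey, which the Allocation concealment section says was done before randomisation (planned size 36 × 40 = 1,440 women). Say whether the target is 7 points or a halving.

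The cost is a rewritten paragraph and a less favourable figure. The restatement changes neither the number of clusters nor the planned analysis. It also gives readers the right yardstick if the result is null.

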### Sampling frame and recruitment

EA, in consultation with VDRC, selected 12 VDCs per district (total of 36 clusters) where it was feasible to carry out project activities and minimize potential contamination. Within the VDC, two wards were randomly selected using probability proportionate to size methodology among eligible wards, defined as having a total household population between 100 and 550, a size assumed appropriate for project activities. Within each ward, a VDRC representative visited ward subdivisions, comprised of approximately 15-20 households to compile a list of households and identify those containing eligible couples based on information from key informants such as female village health workers and where available, existing lists. These household lists were aggregated at the ward level to create the project’s sampling frame.

### Community survey recruitment

For the survey, 40 women per VDC were randomly chosen from the list of households with eligible couples, 20 from each ward were then selected using simple randomization. For this process, within each ward, random numbers were generated in Excel. Households were subsequently organized from highest to lowest based on the randomly generated number. The 20 households with the highest randomly generated numbers were selected for the study. Ten possible replacements were similarly identified given the increased likelihood of ineligible couples based on the reliance on informants and other sources during the creation of the sampling frame.

### LDG participant recruitment and replacement

Using the sampling frame, 10 couples were selected for the weekly LDG sessions with an emphasis on individuals who met the eligibility criteria, lived near the likely site of the LDG group and were willing to commit to weekly participation for 9 months. Replacement of LDG members will occur if a member decides to discontinue participation or if the LDG moderator in consultation with VDRC, EA, and the study PI deem that further participation places the member or another member at risk of violence or other adverse event. Attendance in sessions is monitored weekly to assess “dose” of LDG exposure. Groups with low attendance will receive an in-person supervisory visit from the field monitor and the LDG moderator will follow-up via telephone or in-person with LDG members who are absent to assess barriers to participation and intention to continue.

### FGD recruitment

Family members of LDG members will be recruited for sex-specific FGDs at baseline and again at 9-months post baseline to understand changes in family-based norms on gender equity and IPV, as well as the impact of any project activities and couple-based activism they may have been exposed to. Interested family members will be identified by recommendations made by LDG members. Religious and community leaders will also be recruited into a workshop within which a FGD will be held at the start of the workshop and again 6 months after the conclusion of the workshop to examine changes in their attitudes on gender equity and intimate partner violence, community norms on gender equity and IPV, contextual factors that are occurring in the community, and the community-level impact of the project. Leaders will be identified through recommendations made by stakeholders who are consulted within the study communities.

#### Pair-matching

Each cluster (VDC) was pair-matched based on primary language, caste, percent of literate females per Central Bureau of Statistics (http://www.cbs.gov.np/), and geographic location to minimize contamination. As exact matches are not possible, the final matching procedure was done with VDRC representatives familiar with the local communities best to ensure that the matching process benefited from contextual information not available through public census statistics. Allocation of treatment condition was accomplished by the study Primary Investigator through simple randomization using randomly generated numbers in Excel, with the highest random number per pair being assigned to treatment.

### Allocation concealment mechanisms

Baseline community survey recruitment and administration occurred prior to randomizing study sites in order to minimize bias in recruitment. Further, the informed consent forms did not identify which study-related activities would be implemented in their community. While subsequent survey data collection will inherently come after treatment allocation, the study’s primary outcome stems from the community-based surveys. These individuals will be interviewed by the data collection firm who has no role in the project, enabling the study to keep community survey participants and outcome assessors blind to site allocation. LDG participants cannot be blinded due to the nature of their engagement. Individual recruiters, outcome assessors and data analysts will be blinded to treatment assignment.

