### Population

The study is set in the three districts of Nepal including Nawalparasi, Kapilvastu, and Chitwan. All three districts are over 80% Hindu and have similar profiles in terms of ages at first marriage and levels of female land ownership, but levels of female literacy are more variable (Fig. 2) [16, 17]. These districts were selected because they are located in the region (*terai*) with the highest IPV prevalence,^2^ and these districts are areas in which the local implementing partner, *Vijaya Development Resource Centre* (VDRC), has extensive contacts on the ground and a strong local reputation to facilitate a welcoming and safe atmosphere for the proposed research.

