### Ethics and dissemination

The study adheres to international guidelines for the protection of participants and staff involved in research on violence against women [42] and has a data and safety monitoring plan which details procedures and reporting obligations regarding expected risks and planned protections, confidentiality and data security, and adverse events with oversight provided by an Independent Monitor who is unaffiliated with the study. This study will be stopped prior to its completion if it is associated with adverse effects that call into question the safety of the participants enrolled. Institutional Review Board (IRB) approval has been received from the University of Minnesota, where the PI was based when the study was funded, Emory University, where the PI is currently based, George Mason University where the co-investigator is based and the Nepal National Health Research Council (NHRC). Permission was also received from the District Development Committees representing Nawalparasi, Kapilvastu and Chitwan.

Written informed consent will be sought from all participants prior to randomization, except for activities related to LDG participation for which recruitment occurred after treatment allocation. VDRC field officers who are involved in recruiting will read the statement the because of the significant number of illiterate individuals in Nepal, most of whom are women. Once participants have agreed to participate in the study, the participant and the person obtaining the consent will sign the consent document. Illiterate individuals will be asked to place an “X” instead of their signature. VDRC field officers will obtain informed consent during the recruitment visit. Informed consent will be reaffirmed by the enumerator by reading a summary of participant rights just prior to administering the survey.

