## Discussion

This study seeks to rigorously evaluate a multi-component social norms intervention involving radio, LDGs, and community outreach to reduce IPV. Findings may contribute to the evidence-base for strategies to reduce IPV and to shift gender norms. Despite the numerous strengths of the study design and approach, the limitations of the study must be discussed. As with all RCTs, this study aims to have strong internal validity, as opposed to strong external validity. One specific limitation is that only women who have received support and permission from their husbands to participate in the study will be recruited. While this criterion likely restricts the study from including the most vulnerable women, it is meant to protect women in high-risk situations from exacerbated abuse and protect the research team and other participants from potentially dangerous situations. Another important limitation regarding external validity is that the trial excludes participants with easily detectable physical or cognitive impairments, and growing research has underscored how women with disabilities may be particular to VAWG [45–48]. Thus, the research team is fully aware that those who are restricted from participating may have different profiles than those who are able to join. Another important concern is fidelity of intervention delivery given the number of LDGs and their geographic spread which is bolstered by an extensive monitoring and support plan for LDG facilitators.

The impact of the study may also be difficult to discern due to overlap with programs that have similar content being conducted in the study areas. In order to account for the potential impact of other programming, the study will regularly measure participants’ exposure by polling participants during LDGs and interviews and communicating with key stakeholders in the regions of operation. Intermittent and ongoing disruptions in programmatic activities may possibly occur due to fuel shortages and safety issues pertaining to political tensions. The research team will closely monitor these potential disruptions.

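### Recruiters are declared blind, but the only staff named as taking consent belong to the group that supports the intervention, so blind recruitment at 12 and 18 months is not assured

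*Protocol article*

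**What the plan says.** Under Allocation concealment mechanisms the protocol article declares: "Individual recruiters, outcome assessors and data analysts will be blinded to treatment assignment". The same section says baseline recruitment and interviewing were finished before sites were randomized, to limit recruitment bias. It concedes that later surveys follow allocation and relies there on interviews by a data collection firm with no role in the project.

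Under Ethics and dissemination: "VDRC field officers will obtain informed consent during the recruitment visit". This covers the survey, because the next sentence reads "Informed consent will be reaffirmed by the enumerator by reading a summary of participant rights just prior to administering the survey". The firm's enumerator thus confirms a consent that someone else has already taken. The paragraph opens with: "Written informed consent will be sought from all participants prior to randomization, except for activities related to LDG participation".

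Under Intervention adherence, one monitoring mechanism is: "In-person support and monitoring visits by VDRC field officers to between 4 – 5 LDGs weekly". Table 1 and the Control group section place LDGs in the treatment arm only. The Population section identifies VDRC as the local implementing partner.

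Methods/design describes a repeated cross-sectional trial. The Control group section says a random sample of eligible women is invited at three time points.

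**The concern.** Blind recruitment matters most in a cluster trial when participants are enrolled after clusters have been allocated. A recruiter who knows the arm can, without intending to, differ between arms in whom they persuade, whom they judge ineligible and when they move to a replacement household. The article shows it understands this, since it recruited the baseline sample before randomization for that reason.

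The two follow-up cross-sections carry the primary outcome and lack that protection. The safeguard offered for them, independent interviewing, protects measurement. It does not reach approach, eligibility confirmation, consent or use of replacements. If those steps differ by arm, measured IPV prevalence differs by arm with no true effect. Neither intention-to-treat analysis nor the planned mixed model can recover women who were never enrolled.

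**Working it through.** **Setting the statements side by side**

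1. Recruiters are blind to arm (Allocation concealment mechanisms).
2. VDRC field officers make the recruitment visit and take consent (Ethics and dissemination). No other recruiter is named for the survey.
3. VDRC field officers visit LDGs every week (Intervention adherence), and LDGs run only in treatment VDCs (Table 1).
4. Fresh samples are recruited at 12 and 18 months (Methods/design; Control group), after allocation.

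For follow-up, statement 1 is compatible with 2 to 4 only if the officers who recruit are kept apart from those who visit LDGs and from knowledge of where LDGs run. The article describes no such separation.

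The consent statement fails on its own terms. A woman first sampled at 12 or 18 months cannot have consented before randomization. Treating the survey as a cohort would rescue that sentence but contradict the repeated cross-sectional design, so a correction is needed on either reading.

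**The plan's benchmark**

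Inputs from Sample size and power: 36 VDCs (g = 18 per arm), m = 40 women each, SD 0.25, ICC 0.05, over-time group-level correlation r = 0.40, 80% power, 5% two-sided alpha.

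- Variance of a cluster mean: 0.25² × 0.05 + 0.25² × 0.95/40 = 0.003125 + 0.001484 = 0.004609.
- Detectable difference in change: (1.960 + 0.842) × √(4 × 0.004609 × (1 − 0.40)/18) = 2.802 × 0.0248 = 0.0695.

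This reproduces the stated 7 points.

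**Illustration of scale (loss rates assumed; the article gives none)**

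Let true prevalence be 14% in both arms. In one arm, a fraction q of IPV-exposed women is additionally not enrolled, and no unexposed women are lost. Measured prevalence in that arm is 0.14(1 − q)/(0.14(1 − q) + 0.86).

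| q | Measured prevalence | Shift | Share of 7 points |
|---|---|---|---|
| 10% | 0.126/0.986 = 12.8% | 1.2 points | 17% |
| 20% | 0.112/0.972 = 11.5% | 2.5 points | 35% |

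Losing only exposed women is the extreme form. If 20% of exposed and 10% of unexposed women are lost, prevalence is 0.112/(0.112 + 0.774) = 0.112/0.886 = 12.6%, a shift of 1.4 points. If the same share of both is lost, the shift is zero. If unexposed women are lost preferentially in the treatment arm, the sign reverses and a real benefit is hidden.

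**The case against.** The strongest reply is that the article never says who recruits the follow-up samples. The consent paragraph opens with consent before randomization, so its VDRC recruitment visit can be read as the baseline visit, when nobody could know the allocation. Follow-up logistics may sit in the full protocol or the field manual. This stands in part: VDRC recruitment at 12 and 18 months is an inference from a general passage in the future tense. It does not rescue the text. On that reading the article still asserts that recruiters are blind and that all participants outside LDG activities consent before randomization, and the second assertion remains false for women sampled later.

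Several stronger conclusions are tempting, and the documents do not support them:

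- **The same individuals recruit survey women and visit LDGs.** Only the staff category is shared.
- **The sampling frame is arm-dependent because VDRC compiled it through informants.** The listing is described in the past tense and fed a baseline survey completed before randomization. Replacement households were also chosen by random number. Whether the lists are rebuilt for follow-up is not stated.
- **Husbands' permission filters women differently by arm.** The Discussion says "only women who have received support and permission from their husbands to participate in the study will be recruited", but as a limit on external validity applying to both arms. Nothing says the intervention changes permission. If husbands became more permissive, more high-risk women might enter the treatment sample, which would work against the intervention.
- **Bias of a known size favours the intervention.** Nothing indicates that recruiters know a woman's IPV status before the interview.

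Existing safeguards also count: random household selection, consent forms that do not reveal which activities a community receives, and independent interviewers. They narrow the route for bias. They do not blind a recruiter who already knows where LDGs run.

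**Conclusion.** The point holds as an internal contradiction with a consequence for the primary outcome. As written, recruiter blinding at 12 and 18 months is not assured, and the claim that consent precedes randomization cannot be true for newly sampled women. The baseline sample is unaffected.

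The documents show exposure to arm-dependent selection, not its occurrence. Size and direction are unknown. The 1.2 to 2.5 points (17% to 35% of the 7-point target) are an upper-end illustration. They rest on assumed losses of 10% to 20%, confined to IPV-exposed women in one arm. A reader should not take them as an estimate, nor infer that VDRC staff have selected or will select women by arm.

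The matter still deserves action before follow-up recruitment, because analysis cannot repair selective enrolment afterwards and prevention is cheap.

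**What to change.** For the 12- and 18-month surveys:

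1. Draw the sample and an ordered list of random replacements centrally, from the ward lists compiled before randomization.
2. Have the independent data collection firm, or staff with no LDG role, make the recruitment visit, confirm eligibility and take consent.
3. Record ineligibility, refusal and replacement for each VDC and wave, and report the counts by arm.
4. Correct the recruiter-blinding statement to say who recruits at each wave and what they know. Limit the statement on consent before randomization to the baseline survey.

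As a separate wording point, reconcile the husband-permission condition in the Discussion with the survey eligibility list, which does not contain it.

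The cost is modest: a task moves to a firm already engaged for the interviews, the field manual changes, and a short recruitment log is added. The downside is that couples who arrived after the baseline listing are not sampled, so the follow-up surveys describe the listed population rather than all current residents.
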